#### Secondary analysis

The secondary analysis will involve estimation of effects on a range of outcomes discussed previously for the full year-group cohort samples (years 8 and 9) and for SEND pupils only (years 8 and 9).

Table 3 sets out the secondary analysis to be conducted on the full cohort samples. The analysis for years 8 and 9 will appear in separate reports. Hypothesis tests for the treatment effects in each specification will be reported in the form of *p* values and 95% confidence intervals. For the secondary analysis, treatment effect estimates based on continuous outcomes will be reported as effect sizes (Hedges’ *g*), where outcomes are binary as relative risk ratios and for count outcomes as incident rate ratios. Table 4 sets out the secondary analysis to be performed on the SEND only subsamples.

**Table 3 Tab3:** Secondary analysis—model specifications—full cohort samples years 8 and 9 cohorts (as at September 2020)

Dependent variable	Model	Intervention group indicator	Strata indicator	Covariates	Cohort (at 09/20)
**Attainment outcomes**					
**GCSE English language Mark (standardised)**	Linear hierarchical	Yes	Yes	• KS2 Reading raw score at pupil and school levels • Month of birth • Sex • FSM	Year 9
**GCSE English language Mark (standardised)**	Linear hierarchical	Yes	Yes	• KS2 Reading raw score at pupil and school levels • Month of birth • Sex • FSM	Year 8
**GCSE Mathematics Mark (standardised)**	Linear hierarchical	Yes	Yes	• KS2 mathematics raw score at pupil and school levels • Month of birth • Sex • FSM	Year 9
**GCSE Mathematics Mark (standardised)**	Linear hierarchical	Yes	Yes	• KS2 mathematics raw score at pupil and school levels • Month of birth • Sex • FSM	Year 8
**Wellbeing outcomes**					
**Total difficulties (SDQ)**	Linear hierarchical	Yes	Yes	• Total difficulties baseline score • Month of birth • Sex • FSM	Year 9
**Total difficulties (SDQ)**	Linear hierarchical	Yes	Yes	• Total difficulties baseline score • Month of birth • Sex • FSM	Year 8

**Table 4 Tab4:** Secondary analysis—model specifications—SEND only samples years 8 and 9 cohorts (as at September 2020)

Dependent variable	Model	Intervention group indicator	Strata indicator	Covariates	Cohort (at 09/20)
**Attainment outcomes**					
**GCSE Mathematics Mark (standardised)**	Linear hierarchical	Yes	Yes	• KS2 mathematics raw score at pupil and school levels • Month of birth • Sex	Year 9
**GCSE Mathematics Mark (standardised)**	Linear hierarchical	Yes	Yes	• KS2 mathematics raw score at pupil and school levels • Month of birth • Sex	Year 8
**GCSE English Language Grade 1-9**	Linear hierarchical	Yes	Yes	• KS2 reading raw score at pupil and school levels • Month of birth • Sex	Year 9
**GCSE English Language Grade 1-9**	Linear hierarchical	Yes	Yes	• KS2 reading raw score at pupil and school levels • Month of birth • Sex	Year 8
**GCSE Mathematics Grade 1-9**	Linear hierarchical	Yes	Yes	• KS2 mathematics raw score at pupil and school levels • Month of birth • Sex	Year 9
**GCSE Mathematics Grade 1-9**	Linear hierarchical	Yes	Yes	• KS2 mathematics raw score at pupil and school levels • Month of birth • Sex	Year 8
**Attendance and exclusion outcomes**					
**Number of authorised absences in previous school year 2022/2023**	Count negative binomial hierarchical	Yes	Yes	• Number of authorised absences in school year 2019/2020 • Month of birth • Sex	Year 9
**Number of authorised absences in previous school year 2023/2024**	Count negative binomial hierarchical	Yes	Yes	• Number of authorised absences in school year 2019/2020 • Month of birth • Sex	Year 8
**At least one unauthorised absence in school year 2022/2023**	Binary logistic hierarchical	Yes	Yes	• Number of absences in school year 2019/2020 • Month of birth • Sex	Year 9
**At least one unauthorised absence in school year 2023/2024**	Binary logistic hierarchical	Yes	Yes	• Number of absences in school year 2019/2020 • Month of birth • Sex	Year 8
**At least one exclusion from school in school year 2022/2023**	Binary logistic hierarchical	Yes	Yes	• Number of absences in school year 2019/2020 • Month of birth • Sex	Year 9
**At least one exclusion from school in school year 2023/2024**	Binary logistic hierarchical	Yes	Yes	• Number of absences in school year 2019/2020 • Month of birth • Sex	Year 8

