##### Attendance and exclusions outcomes

The WSS Review aims to bring about a change in school culture, promoting an inclusive and supportive environment as well as addressing specifically the needs of children with SEND in the classroom. These needs can often go unmet leading to poor attendance and in some cases exclusion from school. The trial therefore includes three secondary attendance and exclusion outcomes.
Authorised absences: a count of the number of authorised absences in the relevant school year depending on the cohort being considered.Unauthorised absences: a binary dependent variable for each pupil coded to ‘1’ where an unauthorised absence is observed in the relevant school year, ‘0’ otherwise.Exclusions (temporary fixed term, permanent): a binary dependent variable for each pupil capturing whether exclusions from school were recorded in the relevant school years.

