##### Attendance and exclusions

Analysis of attendance and exclusions outcomes will be adjusted on the basis of baseline measures of attendance for the school year 2019/20 (noting the shortening of the school year due to the Covid-19 pandemic and the closure of schools). These measures relate to the period of time prior to randomisation, which will take place in June 2021. The covariate will be derived by summing the total number of absences (both authorised and unauthorised) for each pupil for the school year 2019/20.

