## Statistical methods

### Statistical methods for primary and secondary outcomes {20a}

Both primary and secondary analysis will follow the intention to treat principle.

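### The authorised-absence count is reported as a rate ratio with no exposure term listed, so the ratio can shift against the intervention if time on roll differs by arm

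*Protocol article*

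**What the plan says.** The protocol article's Attendance and exclusions outcomes section defines the outcome as "a count of the number of authorised absences in the relevant school year depending on the cohort being considered". Table 1 crosses the measures of authorised and unauthorised absence, but this section and Table 4 agree that authorised absence is the count.

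Table 4 (SEND pupils only) fits the count by hierarchical negative binomial regression, separately for each cohort; the dependent variable for the year 9 cohort is "Number of authorised absences in previous school year 2022/2023". It lists an intervention indicator, a strata indicator, "Number of authorised absences in school year 2019/2020", month of birth and sex. The Secondary analysis section says that effects will be reported "for count outcomes as incident rate ratios".

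The Outcome data section under {18a} has absence and exclusion data taken from school systems when GCSE grades are extracted. It does not mention possible sessions, on-roll dates or the treatment of pupils who leave during the year. On the analysis population, section {20a} says: "Both primary and secondary analysis will follow the intention to treat principle".

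The Objectives {7} and Theory of change sections expect the intervention to reduce exclusions, and the latter names permanent ones. For the baseline year the article adds the caveat "noting the shortening of the school year due to the Covid-19 pandemic and the closure of schools" but gives no denominator.

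**The concern.** A rate ratio compares events per unit of time at risk. Without an exposure term, a negative binomial model compares mean counts per pupil. The two agree only if average time at risk is the same in both arms.

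This trial has a specific reason to doubt that. Permanent exclusion ends a pupil's time at the school, it is part of a trial outcome, and the intervention is meant to reduce it. The model is fitted to SEND pupils, whom the Background section describes as disproportionately likely to be excluded. If a pupil who leaves mid-year keeps the count accrued up to then, that pupil looks like a good attender. A school that retains such a pupil records more absences. A programme that succeeds in preventing exclusion could then appear to do worse on authorised absence, with no change in pupils' rate of absence while on roll.

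**Working it through.** **Plan's own figure.** The article gives no power, rate or expected effect for authorised absence, so there is nothing to reproduce for this outcome.

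**Inputs.** From the article: raw school-year count, negative binomial model, the covariates above, 160 schools allocated 1:1, about 25 SEND pupils per school and cohort. Assumed, because the article is silent: the share of pupils leaving during the outcome year in each arm (pC control, pI intervention), the fraction f of the year that leavers are on roll, and the absence rate k of leaving-prone pupils relative to others.

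**Step 1: leavers with ordinary absence rates (k = 1, f = 0.5), no true effect.** The ratio of mean counts is (1 − 0.5·pI)/(1 − 0.5·pC).
- 3% v 2%: 0.990/0.985 = 1.005
- 6% v 3%: 0.985/0.970 = 1.015
- 10% v 5%: 0.975/0.950 = 1.026

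**Step 2: equal leaving.** With pI = pC the numerator equals the denominator and the ratio is 1.000, whatever the level.

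**Step 3: leavers with above-average absence.** Let a share pC of pupils in each arm be leaving-prone, and let only pI of them leave in the intervention arm. The mean count is (1 − pC) + k·f·pC in control and (1 − pC) + k·[(pC − pI) + f·pI] in intervention. For 10% v 5% with k = 3:
- f = 0.5: (0.90 + 0.15 + 0.075)/(0.90 + 0.15) = 1.125/1.050 = 1.071
- f = 0.25: (0.90 + 0.15 + 0.0375)/(0.90 + 0.075) = 1.0875/0.975 = 1.115

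**Step 4: simulation of the offset.** Counts were simulated for 160 schools × 25 pupils, 200 runs per scenario, no true effect. Assumed values were a mean of 12 absences, dispersion 1, a school-level SD of 0.2 on the log scale, and leavers on roll for a uniform fraction of the year. The fitted model was negative binomial with allocation only.

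| Leaving, control v intervention | Ratio without offset | Ratio with log(time on roll) offset |
|---|---|---|
| 5% v 5% | 1.004 | 1.004 |
| 10% v 10% | 1.002 | 1.003 |
| 5% v 2.5% | 1.013 | 1.001 |
| 10% v 5% | 1.024 | 0.998 |

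The simulation error on these ratios is about 0.003. The SD of the estimated log ratio was about 0.045 to 0.050, so the largest shift in the table is roughly half a standard error under these assumptions.

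**Step 5: does the offset also work when leavers have higher rates?** Take 10% v 5%, f = 0.5, k = 3, mean 12, dispersion 1. With an offset, the fitted rate r in each arm solves Σ (y − rT)/(1 + rT) = 0, where T is time on roll.
- Control: 0.90(12 − r)/(1 + r) + 0.10(18 − 0.5r)/(1 + 0.5r) = 0 gives r ≈ 14.27.
- Intervention: 0.90(12 − r)/(1 + r) + 0.05(36 − r)/(1 + r) + 0.05(18 − 0.5r)/(1 + 0.5r) = 0 gives r ≈ 14.33.
- Ratio: 14.33/14.27 ≈ 1.005, against 1.071 without the offset.

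Over assumed means of 3 to 20 and dispersions of 0.5 to 2, the ratio with the offset lies between about 1.00 and 1.02. With Poisson weighting it would be (1.125/0.975)/(1.050/0.950) = 1.154/1.105 = 1.044.

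**The case against.** **The article may simply be condensed.** An offset is a detail that a full protocol or analysis plan could hold, and Table 4 has no column for one. Incident rate ratio is also the usual name for an exponentiated negative binomial coefficient. So the article does not show that an offset has been ruled out. It does fix the outcome as a raw count, list the model terms and name the effect measure, and these do not together give a rate. The extra field also has to be requested with the extract, so it should be settled before then.

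**A reader might infer that the ratio is biased as planned.** The documents do not support that. Bias needs time on roll to differ by arm. Fewer exclusions is the trial's hypothesis, not a known fact.

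**A reader might infer that leavers will be credited with low counts.** The article does not say that partial counts are kept. Data drawn from school systems at GCSE time may leave these pupils missing, which falls under the missing-data provisions of section {20c}. Intention to treat only means that they are not explicitly dropped.

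**A reader might extend the point to the 2019/2020 baseline.** That count precedes randomisation, so allocation cannot affect it. Uneven exposure there can cost precision but cannot bias the ratio in this way.

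**The offset has its own drawbacks.** Time on roll is measured after randomisation, so the offset changes the estimand from absences per pupil to the absence rate while on roll. That stands and should be stated. The further objection, that the offset leaves much of the distortion when leavers have high absence rates, is true of Poisson weighting (1.044). It largely fails for the planned negative binomial model (about 1.005 at the values in Step 5).

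**Conclusion.** The point holds conditionally. The article specifies a raw count and a model with no exposure term listed, and calls the result a rate ratio, in a trial whose intervention is expected to lengthen time on roll by preventing permanent exclusion. If partial counts are kept and exclusion does fall, the ratio can move upward, against the intervention.

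All sizes rest on assumed leaving rates. With leavers on roll for half the year and ordinary absence rates, the shift is about 0.5% (3% v 2%) to 2.6% (10% v 5%). It reaches about 7% at 10% v 5% if leavers have three times the usual rate, and about 12% if they are also on roll for only a quarter of the year. The upper figures need a high leaving rate that the intervention halves. With equal leaving the shift is nil.

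This is a worthwhile refinement to one SEND-only secondary outcome. It is not a threat to the trial's main conclusion.

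**What to change.** - Ask FFT to include each pupil's possible sessions, or on-roll start and end dates, for the outcome year (2022/2023 or 2023/2024) in the absence extract already planned.
- Enter log(possible sessions) as an offset in the hierarchical negative binomial model, and include part-year pupils with their observed sessions.
- State that the estimand is the rate of authorised absence while on roll. Treat pupils with no outcome-year sessions as missing data, since an offset cannot help them.
- Optionally, express the 2019/2020 covariate per possible session. This affects precision only.

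The cost is one extra field and one model term, with no further data collection from pupils. That schools hold possible sessions alongside absence records is an assumption to confirm with FFT.

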#### Baseline measures

Baseline measures will be used for adjusted analyses of trial data for both primary and secondary outcomes. Where possible for each primary and second outcome, a pre-randomisation measure on the same outcome will be obtained in order to form a baseline covariate in the relevant analyses.

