#### Baseline data

FFT will also collect baseline data from Aspire and non-Aspire schools as the basis for adjusted analyses of trial data for both primary and secondary outcomes. Where possible for each primary and secondary outcome, a pre-randomisation measure on the same outcome will be obtained in order to form a baseline covariate in the relevant analyses.

This includes the following:
Raw test scores in Reading and Mathematics at KS2 for each enumerated pupil in Years 8 and 9 at September 2020.Absence and exclusion data for each pupil for the school year 2019/2020.Additional baseline data items (date of birth, sex, FSM status, SEND (ECHP or support), Primary identification of need, current class for English (at September 2020).

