#### Primary analysis

Focusing first on the primary analysis, statistical estimates of the effect of exposure on marks at GCSE English will be obtained from a hierarchical linear model (the estimator), in which pupils are clustered within schools. This model will be fitted to data for SEND pupils only. Three regression model specifications are proposed, where the standardised or equated mark for each pupil is the dependent variable^1^, and the regression models include the following covariates:
*Model 1*: binary intervention group indicator coded to ‘1’ if the school is assigned to the intervention ‘0’ otherwise, plus regional fixed effects (representing strata).*Model 2*: As above, with KS2 Reading raw score as a covariate expressed as a departure from the school mean for each pupil at the pupil level, and as a school average departure from the overall mean at the school level*Model 3*: As model 2, with additional covariates representing sex, month of birth, unauthorised absences in the year prior to randomisation and FSM variables.

The effect size, consistent with Hedges’ *g*, will be obtained from model 2, as set out in EEF guidance [20]. The effect size parameter is written:
$$ ES=\frac{\mu^T-{\mu}^c}{\sqrt{\sigma_i^2+{\sigma}_j^2}} $$

A sample estimate of *μ*^*T*^ − *μ*^*c*^, where *μ*^*T*^ is the mean of the outcome in the treatment group and *μ*^*c*^ the mean in the control group, is derived from the coefficient obtained on the binary intervention group indicator from model 2 above. The denominator $$ {\sigma}_i^2+{\sigma}_j^2 $$, where *i* indexes for the school and *j* the pupil, are the variances at the school and pupil levels respectively, such that the intraclass correlation coefficient is $$ {\sigma}_i^2/{\sigma}_i^2+{\sigma}_j^2 $$. A sample estimate for the denominator is obtained from the total unconstrained pooled variance as described in Hedges [20], who also provides an equation for the variance of the sample estimate for the effect size. Uncertainty will be assessed through computation of 95% confidence intervals and *p* values.

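### Table 4 adjusts the exclusion and unauthorised-absence models for total 2019/20 absences only, although each outcome's own baseline is collected and the protocol says it will be used where possible

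*Protocol article*

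**What the plan says.** The general rule stands in two places in the protocol article. Under Baseline data it reads: "Where possible for each primary and secondary outcome, a pre-randomisation measure on the same outcome will be obtained". Under Baseline measures it is given as "a pre-randomisation measure on the same outcome will be obtained in order to form a baseline covariate in the relevant analyses", with the same where-possible qualifier. The section Additional baseline data items follows the same idea: its adjusted specifications use a baseline of the dependent variable, at pupil level in (b) and at pupil and school levels in (c).

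The data to be collected include "Absence and exclusion data for each pupil for the school year 2019/2020".

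The specific rule, under Baseline measures, Attendance and exclusions, is: "The covariate will be derived by summing the total number of absences (both authorised and unauthorised) for each pupil for the school year 2019/20". It notes that the pandemic shortened that school year.

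Table 4 fixes the covariates row by row. The authorised-absence count model uses "Number of authorised absences in school year 2019/2020". The unauthorised-absence and exclusion models, in both cohorts (four rows), use "Number of absences in school year 2019/2020". Each row also lists month of birth and sex.

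Under Primary analysis, Model 3 for the primary outcome includes "unauthorised absences in the year prior to randomisation and FSM variables".

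**The concern.** For exclusion, the listed covariate measures something other than the outcome. Previous exclusion is the natural predictor of later exclusion and is due to be collected, yet no listed model uses it. For unauthorised absence, defined as "a binary dependent variable for each pupil coded to ‘1’ where an unauthorised absence is observed in the relevant school year", the covariate does contain the outcome's own baseline, but added to authorised absence.

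There is also a direct conflict. The covariate definition prescribes the summed total for this family of outcomes, whereas Table 4 uses authorised absences alone for the count model. An analyst cannot follow both. In an open-label trial whose researchers know the allocation, the covariate should not be left to be settled once outcomes are in hand.

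Reducing absences and exclusions is a stated objective, so these models matter even though they are secondary. At stake are precision and the correction of chance baseline imbalance.

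**Working it through.** **1. The text, side by side**

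| Outcome (Table 4) | Own baseline available? | Covariate under Attendance and exclusions | Covariate in Table 4 | Own baseline used? |
|---|---|---|---|---|
| Authorised absences (count) | Yes | Summed total | Authorised absences | Yes, but conflicts with the definition |
| Any unauthorised absence | Yes: a component of the total, and separate in Model 3 | Summed total | Total absences | Only blended with authorised absence |
| Any exclusion | Yes: listed under Baseline data | Summed total | Total absences | No |

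The where-possible qualifier does not explain the last two rows, because the measures are to be collected. The short school year does not explain them either: it affects total absences too, and the document does not give it as a reason.

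**2. The protocol's own power figure**

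The only power figure for SEND pupils is the primary MDES of 0.20. Inputs from Table 2: J = 160 schools, n = 25, ICC ρ = 0.20, correlations 0.70 (pupil) and 0.32 (school), so R² = 0.49 and 0.1024; P = 0.5.

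MDES = M × √[ρ(1−R²_school)/(P(1−P)J) + (1−ρ)(1−R²_pupil)/(P(1−P)Jn)], with M = t(0.975) + t(0.80) on J−3 = 157 df.

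- School term: 0.20 × 0.8976 / 40 = 0.004488
- Pupil term: 0.80 × 0.51 / 1000 = 0.000408
- MDES = 2.82 × √0.004896 = 0.197, which rounds to the stated 0.20.

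This concerns GCSE marks and is not affected by the point made here.

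**3. A linear illustration for the binary outcomes (assumed inputs)**

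The document gives no event rate, ICC or baseline–outcome correlation for absence or exclusion. Use the same formula with J = 160, n = 25 and no school-level R². Suppose that a better-matched covariate raises pupil-level R² from 0.02 to between 0.10 and 0.20.

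| Assumed ICC | MDES at R² 0.02 | MDES at R² 0.10 to 0.20 |
|---|---|---|
| 0.02 | 0.108 | 0.105 to 0.101 |
| 0.05 | 0.132 | 0.129 to 0.126 |
| 0.10 | 0.164 | 0.162 to 0.160 |

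The MDES falls by about 1–6%. Squaring the ratios, the variance falls by about 2–12%.

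**4. Simulation for exclusion (all inputs assumed)**

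160 schools × 25 pupils, Poisson regression with school-clustered errors, 60 simulated trials per setting, school SD 0.6 on the logit scale. Entries are the variance of the log risk ratio relative to adjusting for absences only.

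| Baseline exclusion rate | Correlation of school effects, 2019/20 to outcome year | + baseline exclusion | + its school mean as well |
|---|---|---|---|
| 14% | 1 (identical) | 0.82 | 0.74 |
| 14% | 0.5 | 0.91 | 0.89 |
| 14% | 0 | 1.00 | 0.99 |
| 2–3% | 0.3–0.5 | 0.98–0.99 | 0.97–0.99 |

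A separate run over baseline rates of 5–14%, school SD 0.3–0.6 and school-effect correlation 0.5–0.8 gave reductions of 2–10% and 2–12%. The most favourable run (14% baseline rate, pupil correlation 0.25, 80 trials per scenario) gave mean standard errors of 0.0912 with absences only, 0.0815–0.0829 with baseline exclusion, and 0.0769–0.0779 with its school mean as well. The squared ratios are 0.80–0.83 and 0.71–0.73. Gains of that size were approached in the other runs only when school effects were identical in the two years.

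The variance reduction therefore runs from about 0% to 29%.

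**The case against.** The strongest reply is that the general rule is qualified and the specific section makes a declared choice: attendance and exclusion outcomes are adjusted for baseline attendance, and Table 4 agrees for both binary outcomes. That stands as a description, but not as a justification. No reason is given for leaving out collected measures, and the same section conflicts with Table 4 on the count model.

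The second reply is that the gain may be small, and this stands. The lag is three school years for the year 9 cohort (2019/20 to 2022/23) and four for the year 8 cohort (to 2023/24), starting from a year cut short by closures. Pupils are enumerated on 1 September 2020, so a pupil permanently excluded from a school in 2019/20 would largely be missing from that school's list, and baseline exclusions would mostly be sparse fixed-term events. At a rare baseline rate the gain nearly vanishes. The simulations also use a marginal Poisson model, not the hierarchical logistic model that Table 4 specifies.

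For unauthorised absence the total already contains the relevant component, and no gain has been quantified.

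The lack of a school-level baseline term is not a clear fault. Specification (c) and the attainment rows have one, but the SDQ rows in Tables 3 and 4 do not.

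**Conclusion.** The inconsistency holds on the text, most clearly for exclusion and less strongly for unauthorised absence. It is a low-cost improvement to secondary, SEND-only models, together with a contradiction that needs reconciling.

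Three stronger conclusions might be inferred and are not supported:

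- **Biased effect estimates.** Allocation is randomised, so a weaker covariate costs precision and correction of chance imbalance but introduces no systematic bias.
- **Damage to the trial's power statement.** The MDES of 0.20 concerns the primary outcome. It reproduces and does not change.
- **A gain worth 20–40% more schools.** Inverting the most favourable variance ratios (1/0.83 = 1.20; 1/0.71 = 1.41) gives that range. It needs a baseline exclusion rate of about 14% and school effects that persist almost fully over three to four years. The document supports neither assumption.

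The defensible statement is a variance reduction for exclusion of between about 0% and somewhat under 30%, wholly dependent on assumed values. The textual finding does not depend on where in that range the truth lies.

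**What to change.** In Table 4:

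- **Exclusion models:** add baseline exclusion (any or none in 2019/20).
- **Unauthorised-absence models:** add baseline unauthorised absence in 2019/20.
- **Authorised-absence count models:** keep authorised absences in 2019/20.

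Total absences may stay in the two binary models as an additional covariate. A school-level mean of each baseline, in line with specification (c) under Additional baseline data items, is optional.

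Amend the covariate definition under Baseline measures, Attendance and exclusions, so that it names these covariates instead of one summed total. If the investigators prefer total absences, for example because exclusions in the shortened year are too sparse, they should state that reason and still resolve the conflict over the count model. Either way, settle it before outcome data are seen.

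The cost is wording only, because the data are already in the planned baseline extract.

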#### Outcome data

In order to obtain attainment data, schools in the trial will be approached by FFT and asked for the marks and grades obtained by individual students at GCSE and provided to the school by exam boards. Data will be obtained at September 2023 (for pupils in year 9 at September 2020), and September 2024 (for pupils in year 8 at September 2020). The measures of Grade achieved by pupils will be equivalent to those available through the National Pupil Database (NPD).

At the point GCSE Grades are extracted from school data systems by FFT, absence and exclusion data will be obtained for pupils for the school year 2022/2023 for year 9 pupils (at September 2020) and the school year 2023/2024 for year 8 pupils (at September 2020).

FFT will also co-ordinate administration and data collection of wellbeing data, measured using the self-reported Strengths and Difficulties Questionnaire (SDQ) for 11–17-year-olds. The SDQ contains 25 items, 20 of which form four sub-scales: emotional symptoms, conduct problems, hyperactivity/inattention and peer problems. A score on each sub-scale is obtained and then the total number of difficulties derived from summing across the subscales. The additional five items form a separate prosocial behaviour scale which we are not intending to use in our analysis. The validity and reliability of the SDQ are discussed in Goodman & Goodman [17, 18].

Prior to randomisation (in June 2021), the SDQ will be administered online to the enumerated sample of pupils (overseen by teachers and teaching assistants) in both years 8 and 9 at baseline. The SDQ will again be administered at June/July 2022 (for year 9s) and June/July 2023 (for year 8s). The choice of timing of the follow-up SDQ measurements was informed by the need to avoid administering the instrument in year 11, when there are significant calls on teachers’ time and school resources in general. Doing so also provides the possibility of using well-being as a mediating variable in analyses of attainment [19], thereby taking into account the required temporal ordering of measurements to permit this.

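### The exclusion outcome includes permanent exclusion but counts only the final school year, so permanent exclusions before that year are never events; baseline exclusions are collected but not used in the exclusion models

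*Protocol article*

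**What the plan says.** The section on attendance and exclusions outcomes names both fixed-term and permanent exclusion and describes "a binary dependent variable for each pupil capturing whether exclusions from school were recorded in the relevant school years". Table 1 words the same outcome for a single year. Table 4, which covers SEND pupils only, has "At least one exclusion from school in school year 2022/2023" for the year 9 cohort and "At least one exclusion from school in school year 2023/2024" for the year 8 cohort.

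The data request matches Table 4. Under Outcome data, "absence and exclusion data will be obtained for pupils for the school year 2022/2023 for year 9 pupils", with 2023/24 for the year 8 cohort. The timing and source are given as "At the point GCSE Grades are extracted from school data systems by FFT".

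Delivery falls earlier. Intervention description {11a} starts training in July 2021 and ends with a second support visit between March and June 2022. Interim analyses {21b} expects school actions from September 2021.

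On baseline, the section Baseline measures sets a rule, qualified by feasibility: "a pre-randomisation measure on the same outcome will be obtained in order to form a baseline covariate in the relevant analyses". The Baseline data section lists "Absence and exclusion data for each pupil for the school year 2019/2020". The baseline section on attendance and exclusions, and Table 4, nevertheless adjust the exclusion models for total absences in 2019/20.

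**The concern.** Permanent exclusion normally ends a pupil's time at the school. A pupil permanently excluded from a trial school before the outcome year cannot become an event there through that exclusion. An outcome defined to include permanent exclusion thus records it only if it happens in year 11. The theory of change expects fixed-term and permanent exclusions to fall before attainment rises, so the unrecorded period is one in which the programme might act.

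There is also a selection problem after randomisation. If the programme keeps some high-risk pupils in school, they can still contribute a final-year event in the intervention arm. Their counterparts in control schools have left the roll and contribute a 0 or nothing. A real benefit would then appear as a slightly higher final-year rate in the intervention arm.

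The covariate point is separate and lighter: a baseline of the same outcome is collected and then left out of the model it suits best.

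**Working it through.** **Window, by cohort** (Interim analyses {21b}, Outcome data, Table 4)

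| Cohort (Sept 2020) | Years from start of school actions to GCSE | Exclusion data requested | Years not observed |
|---|---|---|---|
| Year 9 | 2021/22, 2022/23 | 2022/23 | 2021/22 |
| Year 8 | 2021/22, 2022/23, 2023/24 | 2023/24 | 2021/22, 2022/23 |

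**Coding of a pupil permanently excluded in an unobserved year.** Either the pupil is kept and scored 0 for the final year, or is absent from the school-sourced extract. The event is lost both ways. The first misclassifies it; the second is loss after randomisation in an analysis stated to be by intention to treat.

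**Size.** The article states no exclusion rate and no power figure for this outcome; Table 2 concerns a standardised mean difference in attainment. Every input below except the 4000 is therefore an assumption.

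*Pupils affected.* Table 2 gives 4000 SEND pupils per cohort. If 0.2% to 1.0% were permanently excluded in 2021/22: 4000 × 0.002 = 8 and 4000 × 0.010 = 40.

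*Direction and size of the selection effect.* Let qc and qi be the 2021/22 permanent exclusion risks in control and intervention schools, b = 0.10 the final-year risk of other pupils, and h = 0.50 the final-year risk of pupils spared permanent exclusion. The programme is assumed to halve qc and to do nothing else.

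- Leavers missing: RR = [(1 − qc)b + (qc − qi)h] / [(1 − qi)b]
- Leavers scored 0: RR = [(1 − qc)b + (qc − qi)h] / [(1 − qc)b]
- Permanent exclusions counted as events: RR = [(1 − qc)b + (qc − qi)h + qi] / [(1 − qc)b + qc]

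For qc = 1% and qi = 0.5%:

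- missing: (0.099 + 0.0025) / (0.995 × 0.10) = 0.1015 / 0.0995 = 1.020
- scored 0: 0.1015 / 0.099 = 1.025
- counted: (0.1015 + 0.005) / (0.099 + 0.010) = 0.1065 / 0.109 = 0.977

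| qc to qi | Leavers missing | Leavers scored 0 | Counted |
|---|---|---|---|
| 0.5% to 0.25% | 1.010 | 1.013 | 0.988 |
| 1% to 0.5% | 1.020 | 1.025 | 0.977 |
| 2% to 1% | 1.040 | 1.051 | 0.958 |

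With h = 0.20 instead, the middle row becomes (0.099 + 0.001) / 0.0995 = 1.005, then 0.100 / 0.099 = 1.010, and (0.100 + 0.005) / 0.109 = 0.963. The shift is small throughout, but it crosses 1.

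**Covariates** (Table 4)

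| Model | Baseline covariate, 2019/20 | Same outcome? |
|---|---|---|
| Authorised absences (count) | Authorised absences | Yes |
| Any unauthorised absence | Absences | Partly |
| Any exclusion | Absences | No, although exclusions are collected |

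**The case against.** A single year is a choice made consistently in Table 1, Outcome data and Table 4, and the absence outcomes use the same year. Much of 2021/22 is set-up: plans are first drafted at the October 2021 engagement day and put into effect after the first support visit. For fixed-term exclusions, a year after delivery is a defensible measure of sustained effect. That stands, and the point is limited to permanent exclusion accordingly.

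Four stronger readings are tempting but not supported.

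- *The text contradicts the tables.* One section has "capturing whether exclusions from school were recorded in the relevant school years", in the plural. The two cohorts have different outcome years, so the plural can simply refer to both.
- *Permanently excluded pupils drop out of the trial data.* The article does not say so. The sample is fixed at September 2020, records are linked on pupil identifiers, and sensitivity analyses for missing data are planned. Dropping out is one of two possible codings.
- *The window misses a large share of excluded pupils.* With an assumed yearly risk of 5% to 15% and a between-year correlation of 0 to 0.7, it misses about 20% to 49% of pupils excluded at least once over two years. But this counts any exclusion. At 10% and 0.5 the missed pupils are 14.5 − 10 = 4.5 percentage points, of which permanent exclusions at 0.2% to 1.0% make up at most 1.0 point. The rest are fixed-term exclusions in a year the plan reasonably chose not to measure.
- *The absence covariate biases the estimate.* Under randomisation the choice of baseline covariate affects precision, not validity. The rule on same-outcome baselines is also qualified by feasibility, and 2019/20 was shortened, so baseline exclusions may be sparse. The article prespecifies absences openly. What remains is that exclusions are collected and no reason is given for leaving them out.

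**Conclusion.** The point holds for permanent exclusions. The stated outcome includes them, and the stated window cannot record those in 2021/22, nor those in 2022/23 for the year 8 cohort. How the affected pupils are coded is not stated.

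If the programme prevents such exclusions, and the pupils spared have a higher final-year risk than others, the result is biased against it (if leavers are scored 0, even without that higher risk). The bias is probably small: risk ratios of about 1.01 to 1.05 instead of 0.96 to 0.99 in the main illustration, which rests wholly on assumed rates. The documents do not allow its size to be stated.

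The covariate choice costs precision and departs from the protocol's own rule; it does not bias the estimate. Both parts concern one secondary outcome and leave the primary attainment analysis untouched. The change is worth making because it is cheap, not because the trial's main conclusion depends on it.

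**What to change.** 1. Extract exclusions from September 2021 onwards in the data pull already planned, including records of pupils who have since left the roll.
2. Count any permanent exclusion from a trial school since September 2021 as an event, whether or not the pupil is later on roll, and state this coding.
3. Keep the final-year window for fixed-term exclusions, or report any exclusion since September 2021 alongside it.
4. Add 2019/20 exclusion (any or none) as a covariate in the exclusion models and keep absences, given the shortened year and possibly sparse baseline exclusions.
5. Align the wording of the outcome definition with Tables 1 and 4.

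Cost: one more school year of exclusion data for the year 9 cohort and two for the year 8 cohort, in an extraction that takes place anyway, plus revised wording. The covariate needs no new data.
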